***Baseline measurements***			
Demographic data of participants	Age, gender, educational status, marital status, employment	I	I
Descriptive data of LTC settings	Type of hierarchical organization, care models adopted, family carers' involvement, National Health System information, staff members' roles and education	I	I
***Patient***			
Needs assessment	Camberwell Assessment of Needs in the Elderly (CANE)	R/FC/C	R/FC/C
Level of dependency	Katz Activities of Daily Living index (ADL)	P/C	P/C
*Primary outcome measure*			
Documentation of residents' preferences and of the actions taken to satisfy them	Proportion of residents whose preferences and needs' satisfaction is documented	DR	DR
*Secondary outcome measure*			
Quality of life	Dementia quality of life Instrument (DQoL*)*	R	R
***Family caregivers***			
*Secondary outcome measure*			
Quality of life	EuroQOL	FC	FC
Sense of competence	Sense of Competence Questionnaire (SCQ)	FC	FC
***Professional caregivers***			
*Secondary outcome measure*			
Job satisfaction	Job Satisfaction Questionnaire	C	C
Assessment of the SDM professional attitude	Structured interviews	C	C
*Process measures*			
Assessment of the SDM interview process	Self‐report questionnaire	–	C/FC
Satisfaction with the SDM process; relevance, feasibility and maintenance of the intervention	Self‐report questionnaires	–	R/FC
Barriers/facilitators and influencing factors	Focus group interview	–	C/FC

B, baseline; F1, 6 months after the first SDM interview; P, patient file; C, professional caregiver as informant; I, structured interviews with participants; DR, documentation review; R, residents as informant; FC, family caregiver as informant.

#### b) Phase 1 – Training for professionals

Dementia experts with an expertise in teaching communication skills in the context of clinical care have developed a training for professionals, teaching them how to appropriately stimulate the residents with dementia during the SDM interview to facilitate the expression of their wishes and needs. This training will be provided to the professionals in the intervention wards of both LTC settings. The training programme will focus on the SDM principles in dementia care and active listening (Gordon 2000), to enhance the healthcare professionals' verbal and non‐verbal communication skills to be used to assess, meet and record the residents' needs and preferences during the SDM interview. Participants will receive a 2‐hour weekly training for 5 weeks. Each lesson will be guided by clearly defined learning goals and will be divided into three sessions: theory, role‐playing and feedback sessions.
Theory sessionsDuring these sessions, the healthcare professionals will learn the SDM model, active listening and self‐management principles as a guide to: (1) identify residents' problems or needs; (2) prioritize them, choosing the main needs or problems that will become the goals of the intervention; (3) identify alternatives to meet them; (4) decide and plan the intervention; (5) execute plans and (6) evaluate the outcomes.Role‐playing sessionsDuring these sessions, professionals will practice skills and knowledge acquired in the theoretical part of the lesson. In some cases, the trainer will provide case‐vignettes that will be used as cues to set up role‐play exercises; in others professionals will be asked to report difficult situations they face during their daily work. Moreover, professionals will be invited to bring real care plans, to understand whether SDM is applied and to practice the learning objectives of the training programme in daily care situations.Feedback sessionsThe trainer will support and supervise the professionals during the role‐playing sessions, guide the discussion and provide feedbacks to stimulate reflection on their own professional attitude.

One additional lesson, 3 months after the end of the training, will be organized to discuss the problems professionals faced so far and to refresh some of the core issues of the training.

#### c) Phase 2 – SDM conversation

The SDM conversation will take place between a triad, composed of the resident with dementia, the family caregiver and the LTC professional as facilitator. The professional will be taught to tell the resident and the family caregiver that the aim of the consultation is to tailor the ‘life‐and‐care plan’ to the resident's actual needs and preferences. Using the unmet needs as collected with the CANE, as starting point, the main steps of the SDM process that will be applied during the conversation are: (a) identification of problems and needs; (b) prioritization of the most important problems or needs to set the intervention's goals; (c) discussion of options and preferences and (d) identification of actions. The role of the family caregiver is to support and facilitate the resident's expression: if communication is limited, the family caregiver is stimulated to intervene, to add information and to stimulate the person with dementia. Together, the participants in the consultation will make plans to comply with the prioritized needs and will develop actions to meet them.

#### d) Phase 3 – Implementation of plans

Immediately after the interview, the professional caregiver is asked to update the resident ‘life‐and‐care plan’ with the outcomes of the SDM interview reporting: I. the goals of the intervention based on the resident's problems and needs identified and preferences expressed, II. the planned actions based on the agreed decisions taken and III. the monitoring of the SDM intervention (i.e. the planned actions have been effectively implemented and/or the agreed decisions satisfied).

#### e) Phase 4 – Update

The ‘life‐and‐care plan’ is then updated regularly by the professional caregiver, who will report if all aspects of the intervention are (not) going according to plan.

## Measures

### Participants' details and LTC settings description

Demographics of the participants will be collected together with data on the inner organization and management of the involved LTC settings, considered potential influencing factors regarding the implementation process.

Besides, several valid instruments will be used. For a full description of the data collected and of the tools used (Table 1).

### residents' characteristics

#### Katz index of independence in Activities of Daily Living (ADL)

The Katz ADL (Katz *et al*. 1963) measures the clients' ability to independently perform activities of daily living. The Index ranks adequacy of performance in the six functions bathing, dressing, toileting, transferring, continence and feeding. Lower scores indicate a higher level of dependency. If the Katz index is not reported in the residents' medical record, the information will be gained by asking the units' key nurses or healthcare professionals to complete it. These data will be used as additional information to make a profile of the residents, to better identify and prioritize their main needs to be satisfied.

### Outcome measures

#### Primary outcome measure

The primary outcome measure is the proportion of dementia residents whose preferences, needs and related actions are known, satisfied and documented in their ‘life‐and‐care plan’ (Detering *et al*. 2010). Six months after the SDM interviews, a researcher will determine the compliance with residents' needs and wishes accomplished. The researcher will check the residents ‘life‐and‐care plan’ updated after the SDM interviews by professional caregivers, identifying any documentation of the resident' s needs and preferences, goal set by the triad, actions taken to satisfy it and goal satisfaction (see Phase 3 of the intervention).

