#### a) Pre‐intervention assessment − Dementia residents' (un)met needs assessment

At baseline (Table 1), a trained researcher will administer an adapted version of the Camberwell Assessment of Needs in the Elderly (CANE) (Orrell & Hancock 2004, Orrell *et al*. 2007) to the dementia residents and to the formal and informal caregivers. The CANE is a comprehensive, person‐centred needs assessment tool that has been designed for use with older people: the instrument is based on the principle that identifying a need means identifying a problem plus an appropriate intervention which will help or meet the need. It assesses the older person's needs from various perspectives: to reach this goal, CANE is to be administered not only to the older person but also to a key staff member and to an informal caregiver. The CANE has shown a good validity and reliability (Reynolds *et al*. 2000). In this study, only those items of the Dutch (Van der Roest *et al*. 2008) and Italian (Chattat & Celeste 2008) version of the CANE will be used to assess specific psychosocial needs of dementia persons who live in LTC settings. This was decided after discussion with the involved professionals as they declined the use of the full CANE questionnaire because of its length and relevance for nursing homes. They considered the need to manage behavioural problems, the need for tailored activities and the emotional and social needs as most important for residents with dementia in LTC settings (Cadieux *et al*. 2013). Starting from these data, we tried to improve the study protocol by discussing it with professionals to be involved. The items' relevance for nursing homes was related to a model for nursing home care, the Eden Alternative that aims to provide a person‐centered care environment for older residents (Brownie & Nancarrow 2013). On the basis of its principles, we have selected the CANE items that cover the following psychosocial issues: self‐care; daytime activities; psychological distress; information; behaviour; company and intimate relationship. The outcome of the selected CANE items will be a summary of met and unmet needs. The trained researcher who administers the CANE will share and discuss the information gained with the LTC professionals involved in the study before they will conduct the SDM interviews with the dementia resident and his family caregiver, so that they can use this information as a guidance for the interview. This will facilitate the selection and prioritization of their needs and the identification of possible interventions to meet them.

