## Data analysis

Quantitative data will be analyzed using the Statistical Package for Social Science (SPSS). The proportion of residents whose SDM documentation on needs satisfaction has been fulfilled, will be analyzed using the Fischer's exact test. Secondary outcomes, at the level of residents, professional and informal caregivers, will be calculated using parametric and non‐parametric tests, making comparison between and within groups. Descriptive statistics will be used to compare the experimental and control nursing home wards for socio‐demographic characteristics and baseline variables. In each country, the focus group discussions' content will be translated into English. Two independent researchers will code the data by using a constant comparative method (Johnson *et al*. 2012). Each researcher will develop and label categories with appropriate codes outlining the core concepts of the focus group interviews. Then, the codes will be combined in clusters to define the concepts and identify similarities and differences between the interviews (Boeije 2002). Codings will be discussed until consensus will be reached.

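### The primary-outcome review uses criteria tied to the intervention, so it tends to reveal arm and time point, and the assessor is not kept apart from the researcher who informs the SDM interviews

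*Protocol article*

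**What the plan says.** All references are to the protocol article.

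- **Primary outcome measure.** The outcome is the proportion of residents whose preferences, needs and related actions are known, satisfied and documented. The assessment is timed "Six months after the SDM interviews", when "a researcher will determine the compliance with" residents' needs and wishes. The source is the plan as revised by the professional caregivers following those interviews. The items sought include the "goal set by the triad, actions taken to satisfy it and goal satisfaction", with a pointer to Phase 3 of the intervention.
- **Table 1.** The same outcome is obtained by documentation review at baseline and at follow-up.
- **Pre-intervention assessment.** After the needs assessment, the CANE interviewer "will share and discuss the information gained with the LTC professionals involved in the study before they will conduct the SDM interviews". The stated purpose of this contact is "so that they can use this information as a guidance for the interview".
- **Phases 2 to 4.** The triad conversation produces goals and actions. The professional caregiver enters them in the plan, records whether they were carried out or satisfied, and keeps the plan current.
- **Data analysis.** The primary proportion is tested with Fisher's exact test. For the focus groups, "Two independent researchers will code the data by using a constant comparative method".

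**The concern.** Residents, families and staff know whether an SDM interview took place. The review of the plans is the one step towards the primary outcome where masking is at least partly possible. The published criterion works against it, because it tells the reviewer to look for things that only the intervention creates.

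Two consequences follow. First, the control wards have no triad interview, so they have no triad goal and no interview date from which to count six months. The reviewer must adapt the criterion for them, and in doing so knows the arm. Second, where a note leaves it unclear whether a goal was met, a reviewer who knows the arm can read it more generously in one arm than in the other. The risk grows if that reviewer helped to identify the same residents' needs before the interviews.

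The study is meant to indicate potential effectiveness and to inform a full trial, so an inflated contrast would be carried forward.

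**Working it through.** The article gives no power, significance level or expected effect, so there is no planned figure to reproduce. The check has two parts.

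**1. Does the criterion reveal arm and time point?**

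| Element of the primary outcome review | Where it arises | In control wards? | At baseline? |
|---|---|---|---|
| Clock starts at the SDM interview | Phase 2 | No such interview | No |
| Goal agreed by the triad | Phase 2 | No triad conversation | No |
| Plan revised after the interview | Phase 3 | No | No |
| Satisfaction of that goal | Phases 3 and 4 | Only for goals of other origin | Only for goals of other origin |

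Read literally, each element marks a plan as an intervention-ward follow-up plan. This is stated text and does not depend on what the article leaves out.

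**2. How much could differential leniency matter?**

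Inputs from Subjects and settings: 20 residents per ward and two wards per arm, so 2 × 20 = 40 per arm and 80 in total. Everything else here is assumed.

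*Size of the spurious difference* = share of ambiguous plans × difference in leniency between arms:
- 0.20 × 25 points = 5 points; 0.05 × 40 = 2 residents
- 0.40 × 25 points = 10 points; 0.10 × 40 = 4 residents

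*Effect on the test.* Exact enumeration of Fisher's test, 40 v 40, two-sided 0.05 (assumed), no true effect, residents treated as independent. With X and Y binomial(40) counts for intervention and control, the probability of a significant result favouring the intervention is the sum of P(X = x)·P(Y = y) over all pairs with x > y and p ≤ 0.05. The control rate is p and the intervention rate is p plus the spurious difference:

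| True rate p | No leniency | +5 points | +10 points |
|---|---|---|---|
| 10% | 0.8% | 5.2% | 16.2% |
| 20% | 1.4% | 4.8% | 12.3% |
| 30% | 1.4% | 4.2% | 10.4% |
| 50% | 1.7% | 4.6% | 10.7% |

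*Counts needed for p ≤ 0.05:*
- control 4/40 needs 12/40 (8 extra)
- control 8/40 needs 18/40 (10 extra)
- control 12/40 needs 22/40 (10 extra)
- control 20/40 needs 30/40 (10 extra)

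So 2 to 4 leniently scored plans would not produce a significant result from equal counts. They would raise the chance of one when added to ordinary sampling variation.

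**The case against.** The strongest reply is that a condensed article may leave assessor masking to the full protocol, and that silence is not a defect. That is right as far as it goes. A reader might infer three things that the text does not support:

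- **That the assessor is unmasked.** The article does not say so. It states no masking, and its criteria make masking hard.
- **That the assessor coached the intervention staff.** The CANE researcher shares and discusses findings as interview guidance. Training is a separate component by dementia experts, who "have developed a training for professionals, teaching them how to appropriately stimulate the residents with dementia during the SDM interview". No passage says that the CANE researcher and the assessor are the same person. No passage separates them either. That the discussion takes place only in the intervention wards is itself inferred from its link to the SDM interviews.
- **That there is only one rater.** The wording is singular but does not settle this for two countries. The double coding of focus groups is thematic work, a different task, so the contrast carries little weight.

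Two further objections stand. Much of the task may be a check for the presence of entries in plans with four set sections (Context), and staff who cannot be masked record much of the satisfaction judgement, so masking the reviewer cannot remove that part of any bias. The leniency figures have no source in the article, and this is a feasibility study whose primary objectives are feasibility, acceptability and process.

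None of this answers the point about the criterion. It is written in terms that only the intervention arm can meet, and that is on the page.

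**Conclusion.** The concern holds in limited form. The primary outcome is judged with criteria that tend to disclose arm and time point, no masking is stated, and nothing rules out that the assessor is the researcher who gave the CANE feedback. Bias towards the intervention wards is possible but not demonstrated.

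Its direction and size are unknown. The range of 2 to 4 of 40 residents rests wholly on the assumed 20% to 40% ambiguity and 25-point leniency. The corresponding rise in false-positive probability, from about 1% to 2% up to about 4% to 16%, further assumes a two-sided 0.05 level and independent residents. The change is worth making because the outcome is the study's main quantitative contrast and the remedy is clerical.

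**What to change.** Amend the Primary outcome measure section as follows:

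1. Score both arms and both time points with one fixed, arm-neutral checklist: any documented need or preference, a goal, an action, and recorded goal satisfaction. Do not require that the goal came from the triad.
2. Apply it to copied extracts with ward, staff names, dates and SDM labels removed, mixed in random order within each country.
3. Where existing staffing allows, give the scoring to a project researcher who did not provide the CANE feedback.
4. Record the rater's guess of arm for each extract after scoring, and report how often it was right.

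Cost: copying and redacting at most 80 residents × 2 time points = 160 extracts, and some exchange of tasks among existing researchers. The article does not describe staffing, so step 3 may not be possible in both countries. Masking will be partial, because plan content can still point to the arm. Bias in what unmasked staff write in the plans is not removed and should be named as a limitation. The checklist helps even where masking fails.

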### Context

The study runs within the IMPACT project (Implementation of quality indicators in Palliative Care study) funded by the EU 7^th^ Framework Programme that involves five European countries, among which the Netherlands and Italy. Life‐and‐care plans, as tools for goal planning and for care and registration of treatment actions, are compulsory in both Dutch and Italian LTC facilities. In these settings, a multidisciplinary team assesses residents during the first two weeks following admission. When assessment is completed, a ‘life‐and‐care plan’ is developed and compulsorily signed by the professional responsible for the plan, the family caregiver and if possible the resident. In the Dutch LTC facility, usually a nurse is responsible for the plan and in the Italian setting, a nurse or any available and qualified member of the multidisciplinary team. The structure of the plans adopted in both countries is similar and consists of four main sections: Problems; Goals; Actions; Evaluation. Problem areas primarily cover: mental and physical well‐being; activities of daily living; and cognitive and social functioning. Plans are updated as changes in the resident's condition occur and at least once a year. The choice to develop and implement an SDM framework in care planning in the Netherlands and in Italy was primarily based on the existing collaboration between the University of Bologna and the University of Nijmegen. Second, SDM is an issue that is receiving growing attention in both countries. In the Netherlands, a policy called ‘family participation’ has been developed in the 1990s to promote the participation of family members in the care planning of their relatives admitted into nursing homes (Dijkstra 2007). However, a structured involvement of both family carers and dementia residents by using SDM in LTC settings has not become common practice. In Italy, the National Health Plan developed in 2011 underlines the importance of involving citizens and patients in the healthcare decision‐making process. However, there are only few studies on SDM carried out in this country and none of them was conducted in the dementia care area (Goss *et al*. 2011).

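### The primary outcome is defined for both arms, but its scoring rule and tested endpoint refer to steps done only on the intervention wards, and satisfaction is read from the deliverers' own notes

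*Protocol article*

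**What the plan says.** All places are in the Protocol article.

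- *Primary outcome measure*, first sentence: the outcome is "the proportion of dementia residents whose preferences, needs and related actions are known, satisfied and documented" in the life-and-care plan. Nothing here refers to an arm.
- *Primary outcome measure*, scoring: six months after the SDM interviews, a researcher reads the plan "updated after the SDM interviews by professional caregivers". The researcher looks for needs and preferences, "goal set by the triad, actions taken to satisfy it and goal satisfaction", and the text points to Phase 3 of the intervention.
- *Data analysis*: the quantity tested with Fisher's exact test is "The proportion of residents whose SDM documentation on needs satisfaction has been fulfilled".
- *Phase 1* and *Subjects and settings*: training goes to professionals on the intervention wards, who then conduct the SDM interviews.
- *Phase 3*: "Immediately after the interview, the professional caregiver is asked to update the resident" plan with the goals, the agreed actions, and whether those actions were carried out or the decisions satisfied.
- *Context*: ordinary plans in both countries already have sections for problems, goals, actions and evaluation. They are signed by the professional, the family caregiver and, where possible, the resident. On revision: "Plans are updated as changes in the resident's condition occur and at least once a year".
- *Table 1*: the documentation review is scheduled at baseline and at follow-up (F1). The CANE is also scheduled at both times, from resident, family caregiver and professional. *Subjects and settings* says both groups use the same tools.

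**The concern.** The definition and the scoring rule do not describe the same measurement. The definition can be applied to any resident. The rule names a record, a goal-setting event and a date that exist only where an SDM interview was held. Because the outcome requires several elements together, one element that controls cannot supply is enough to fail them under a literal reading.

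The source of the evidence is a separate problem. A researcher does the scoring, but the record scored is written by the professional who was trained, led the interview and was asked to enter these items. The judgement that a need was satisfied is therefore the deliverer's own report.

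At stake is the study's claim to assess potential effectiveness and to inform a full trial. Part of any between-group difference could come from the scoring rule and not from needs being better known or met.

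**Working it through.** **1. Group sizes.** *Subjects and settings* gives 20 residents per ward and two wards per arm: 2 × 20 = 40 per arm, which matches the stated 40. The article gives no expected rates and no significance level. I assume two-sided 0.05.

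**2. The rule applied to each record.**

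| Element of the scoring rule | Intervention plan at F1 | Control plan at F1 | Any plan at baseline |
|---|---|---|---|
| Plan revised after the SDM interview | Yes, by Phase 3 | No interview held | Interview not yet held |
| Goal set by the triad, as in Phase 3 | Possible | Not in the Phase 3 sense | Not in the Phase 3 sense |
| Six months counted from the interview | Defined | No starting date | Not applicable |
| SDM documentation (*Data analysis*) | Possible | None | None |
| Need or preference, goal, action, evaluation | Possible | Possible in the four usual sections | Possible in the four usual sections |

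Only the last row works in every cell.

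**3. Extreme case.** Assume controls score 0/40. With equal groups the two tails are the same, so for k successes against none, p = 2 × C(40,k) / C(80,k).

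- k = 5: 2 × 658,008 / 24,040,016 = 0.055
- k = 6: 2 × 3,838,380 / 300,500,200 = 0.026
- k = 8: p = 0.005

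So 6/40 (15%) is enough. If four controls were credited, 6 against 4 gives p = 0.74.

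**4. Between the extremes.** Let both arms have the same true success rate p. Credit every intervention success but only a fraction c of control successes. The chance of a significant result is the sum, over all pairs (a, b) with Fisher p < 0.05, of Bin(a; 40, p) × Bin(b; 40, cp). Clustering by ward is ignored. Both p and c are assumptions, since the article gives neither.

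| True rate p | c = 0 | c = 0.25 | c = 0.5 | c = 0.75 | c = 1 |
|---|---|---|---|---|---|
| 0.1 | 20.6% | 9.4% | 4.3% | 2.1% | 1.7% |
| 0.2 | 83.9% | 41.1% | 16.2% | 5.5% | 2.8% |
| 0.3 | 99.1% | 68.2% | 28.1% | 7.8% | 2.8% |
| 0.5 | 100% | 94.6% | 55.9% | 15.4% | 3.3% |
| 0.7 | 100% | 99.8% | 85.9% | 28.5% | 2.8% |

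The last column is an arm-neutral rule. There the false-positive rate is 1.7% to 3.3%, below the nominal 5%.

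**The case against.** The strongest reply is that an arm-neutral measure was plainly intended. The abstract, Table 1 and the first sentence of the outcome section do not tie it to an arm. The review is scheduled at baseline, before any interview, and both groups use the same tools. Usual plans already carry goals, actions and evaluation and are signed by the family. *Study design* describes all subjects as organised in triads, so a goal set by the triad might be read as a goal in a plan those parties signed. The study is also a feasibility study, and more complete recording is one of its stated aims.

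Most of this stands as evidence of intent, and it rules out several stronger readings that a reader might infer:

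- *That controls fail by definition.* This follows only from the literal rule. A reviewer working from the headline definition could credit control plans.
- *That a difference is guaranteed if staff follow instructions.* It is not. Phases 3 and 4 let staff record that an action was not carried out or that a plan is off course, and such a resident would not count as satisfied. For the same reason the outcome is not purely a fidelity measure.
- *That about half of control plans would go unrevised within six months.* This treats the annual revision as the usual one. The text makes it a minimum, alongside revision when the resident's condition changes. An unrevised plan may also already hold the required entries.
- *That the CANE is left unused.* Table 1 repeats it at F1 and *Pre-intervention assessment* says "The outcome of the selected CANE items will be a summary of met and unmet needs". Table 1 does not label it primary or secondary, but its analysis may be set out in a document not shown.

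The reply does not supply a scoring rule for control or baseline plans. The one rule printed points to Phase 3, and the tested endpoint repeats the tie to SDM. Nor does it change who writes the notes on satisfaction.

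**Conclusion.** The concern holds in a limited form. The headline outcome is sound for both arms. The printed scoring rule and the tested endpoint are not, and as written they bias the Fisher comparison toward the intervention. Satisfaction also rests on the deliverers' own records.

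The direction of the bias follows from the text; its size does not. At an assumed common true rate of 30%, the false-positive rate runs from 99.1% if no control success is credited, through 28.1% if half are, to 2.8% if all are. The figure of 6/40 giving p = 0.026 depends on the assumed 0/40 in controls.

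It would go too far to say that the study can reveal nothing about potential effectiveness. Recording preferences is itself an aim, and residents' self-reported quality of life is measured separately.

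**What to change.** 1. In *Primary outcome measure* and *Data analysis*, use one scoring rule that does not mention the SDM interview: a documented need or preference, a goal, an action and an evaluation, found in the plan's four existing sections. Keep preferences in it, because an outcome limited to needs flagged by the CANE would lose them.
2. Apply that rule at baseline and at a matched six-month date in all four wards, with the starting date for control wards stated.
3. Report triad-set goals and SDM entries as fidelity measures in the intervention arm.
4. Name change in unmet CANE needs, with the resident as first informant and the family caregiver as second, as an outcome for satisfaction that does not depend on the professionals' notes.

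The cost is rewording two sections and the form used to abstract the plans. By Table 1 and the same-tools statement, the data are already collected at both times in both groups. The observed difference will probably be smaller. Family informants in the intervention arm took part in the SDM interview and so are not blind to it, which is why the resident's answers should come first.
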